### 2.5. Intervention

Based on conventional treatment, EG1: rehabilitation training synchronized with intradermal acupuncture treatment of the affected upper limb; EG2: rehabilitation training of the affected upper limb synchronized with focal-side scalp acupuncture treatment; EG3: rehabilitation training synchronized with intradermal acupuncture treatment of the affected upper limb synchronized with focal-side scalp acupuncture treatment, i.e., ASRT, the schematic diagram of which is shown in Figure 2, and CG: rehabilitation training of the affected upper limb. Subjects in each group will complete treatment for a fixed period of time, 30 min/session, 1 session/day, with 2 days off after treatment on 5 consecutive days per week for a total of 4 weeks.

**Figure 2 F2:**
[figure not shown]
Schematic diagram of ASRT for upper limb dysfunction in stroke patients (this figure is partially drawn by Figdraw. ID: AYIWY42f22).

#### 2.5.1. Conventional treatment

All patients will receive conventional treatment, including pharmacological treatment and rehabilitation. Pharmacological treatment applies anticoagulation, lipid regulation, blood pressure and blood glucose control, cerebral nerve nutrition, and improvement of cerebral metabolism to control complications and reduce functional impairment (25). Rehabilitation therapy includes movement therapy of the affected lower limb and trunk (neurodevelopmental therapy based on the new Bobath technique, proprioceptive neuromuscular facilitation technique (PNF), nerve stimulant therapy, balance function training, and gait training), physical factor therapy, occupational therapy (mainly ADL training), and speech-swallowing training. The above treatments are individualized and targeted, and appropriate interventions should be selected according to the degree and type of functional impairment of the patient. 5 days per week, for 4 weeks.

#### 2.5.2. Rehabilitation training of the affected upper limb

Individualized functional training will be used for the affected upper limb, which mainly included stretching training (continuous passive distraction to inhibit persistent contraction of spastic muscles), and new Bobath technique (control of key points to inhibit abnormal postural and motor patterns), and the PNF technique.

#### 2.5.3. Intradermal acupuncture treatment of the affected upper limb

*Acupuncture points selection:* Jianyu (LI15), Jianliao (TE14), Jiquan (HT1), Chize (LU5), Quze (PC3), Hegu (LI4), Houxi (SI3), Waiguan (TE5) points on the affected upper limb.

*Acupuncture method:* After sterilization of the acupoints, the granular intradermal needles (0.22 mm × 5 mm, Huanqiu, Suzhou, China.) will be selected, and the skin around the acupoints will be stretched to the sides with one hand, and the needle will be inserted into the acupuncture point subcutaneously by holding the needle handle with forceps in the other hand, then the needle handle will be covered with medical tape to hold the needle in place. The intradermal acupuncture will retain for 30 min, and during the period of needle retention, pressure will be performed every 5 min for 1 min each time.

*Acupuncture removal method:* The physician fixes the skin on both sides of the needle with one hand, removes the adhesive tape with the other hand, and then holds the needle handle with forceps and removes the needle.

#### 2.5.4. Scalp acupuncture treatment of the focal-side head

*Acupuncture points selection:* The middle part of 2/5 of the Anterior Oblique Line of Vertex-Temporal (MS6), from Qianding (DU21) oblique to Xuanli (GB6), and the middle part of 2/5 of the Posterior Oblique Line of Vertex-Temporal (MS7), from Baihui (DU20) obliquely to Qubin (GB7) on the side of the lesion.

*Acupuncture method:* Following routine local disinfection, a disposable stainless steel needle (0.35 mm × 40 mm, Huatuo, Suzhou, China) will be used, and the needle made an angle of 30° with the scalp and will be rapidly stabbed into the subscalp when the tip reaches the epicranial aponeurosis, the needle will be made parallel to the scalp and stabbed 25~35 mm, then the twisting technique will be performed rapidly and continuously, and the twisting speed will be kept at about 150 times per min for 2 min to be the patient to get Deqi sensation (26). The needle will be retained for 30 min, and the twisting technique will be performed every 10 min during the needle retention period.

*Acupuncture removal method:* the physician first slowly out the head needle to the subcutaneous, and then quickly pulls out, pulling the needle with a sterile cotton ball to press the needle hole to prevent bleeding.

### 2.6. Outcome measures

#### 2.6.1. Primary outcome measures

(1) *FMA-UE* will be used to evaluate the patients' upper limb movement function.

This scale is one of the most widely used clinical scales for assessing upper extremity motor recovery after stroke, with 33 items, divided into 3 levels of scores, 0, 1, and 2 points respectively, according to the degree of task completion, and the total score was 66, with higher patient scores suggesting better motor function. FMA-UE is quantified by indicators and has the advantages of being detailed, reliable, and sensitive, which has been established as a standardized assessment tool to measure upper limb movement function (27).

Assessment time points: baseline, and 2 weeks, 4 weeks, 3 months, and 6 months after treatment.

(2) *SEP* will be used to assess the sensory function.

SEP is the potential induced in different parts of the central nervous conduction pathway after the skin or peripheral nerve receives certain pulse electrical stimulation. It has the advantages of high sensitivity, strong specificity, and repeatability (28). As an objective test, it excludes the influence of patient's subjective factors, which makes the evaluation results more reliable; SEP not only provides an objective assessment of stroke limb sensory function and feedback on the therapeutic effect of limb rehabilitation, but also guides the formulation of limb rehabilitation protocols and clinical treatment, and is considered an important reference indicator for predicting the prognosis of stroke limb function (29, 30). The main observations of SEP are latency and wave amplitude, with latency related to the brain white matter and wave amplitude related to axons and cortex. N20 arises in the primary somatosensory cortex and is the first near-field potential of SEP (31). In this study, an EMG-evoked potential device (Dantec, Denmark) will be used for median nerve SEP testing. A saddle stimulating electrode will be placed 2–3 cm above the transverse carpal tunnel of the upper limb on the hemiplegic side of the patient. According to the 10–20 international system of EEG electrode placement (32), the recording electrodes were located at C3' & C4' of the head contralateral to the limb under test, and the reference electrode is placed at Fz. The electrode impedance will be kept below 5 kΩ. Constant current square wave pulses will be used with a frequency set at 5 Hz and a pulse width of 0.2 ms, with a stimulation intensity sufficient to elicit slight thumb movement. Two median nerve N20 SEP examinations will be performed for each evaluation, each time superimposed 200 times, and the latency and wave amplitude of the N20 wave will be recorded, and the average value of the two times will be taken as the final test result.

Assessment time points: baseline, and 4 weeks after treatment.

#### 2.6.2. Secondary outcome measures

(1) *WMFT* will be utilized to evaluate upper extremity motor function, the WMFT scale contains 15 assessment tasks, items 1–7 mainly test single-joint motor function, and items 8–15 test the ability of multiple joints to move. Each item is divided into 6 levels of scoring according to the degree of task completion, with a maximum score of 5 and a minimum score of 0. The total score is 75. Higher scores tend to indicate better upper limb motor function. This scale not only evaluates the quality of the patient's task completion but also provides a record of the time of task completion. It has been demonstrated to be highly reliable and valid for assessing upper extremity motor dysfunction after stroke (33).

Assessment time points: baseline, and 2 weeks, 4 weeks, 3 months, and 6 months after treatment.

(2) *UEFT* will also be used as a scale to evaluate upper limb motor function in this trial. This scale contains 33 activities, which are divided into categories I~VI, of which categories I ~IV mainly check the grasping and finger-pinching functions of the hand and categories V~VI mainly assess the overall function and coordination of the upper limbs. Each activity was divided into four levels, with a score of 0 indicating that all activities could not be completed; a score of 1 indicating that only part of the activities could be completed; a score of 2 indicating that the activities could be completed, but the movements were slow or clumsy; and a score of 3 indicating that the activities could be completed normally (34).

Assessment time points: baseline, and 2 weeks, 4 weeks, 3 months, and 6 months after treatment.

(3) *The Chinese version of reNSA* will be used to assess upper limb sensory function, which includes the sensory of light touch, temperature, pinprick, pressure, and proprioception in the shoulder, elbow, wrist, and hands, and stereognosis in both hands. Light touch, temperature, pinprick, and pressure sensation were divided into 3 levels, for a total of 64 points; proprioception was divided into 4 levels (0–3 points), for a total of 24 points. Stereognosis was assessed by asking patients to perceive different objects placed in their hands, a total of 10 points. Yang et al. conducted cross-cultural adjustment and reliability and validity tests of the scale and noted that the Chinese version of reNSA can be used to assess the sensory function of stroke patients and provide an objective basis for rehabilitation planning (35).

Assessment time points: baseline, and 2 weeks, 4 weeks, 3 months, and 6 months after treatment.

(4) *DTI* will be used to predict upper extremity movement function, which is a non-invasive magnetic resonance imaging technique that effectively observes and tracks the alignment and direction of white matter fiber tracts and the coherence and integrity of myelin sheaths by quantitatively assessing the differences in diffusion information of water molecule in brain (36), and can acutely track the changes in white matter microstructure of the brain (37). Studies have shown that injury of the posterior limb of the internal capsule (PLIC) is significantly associated with the prognosis of upper limb motor function (38). In this study, the Fractional anisotropy (FA) of the corticospinal tract of the PLIC will be measured on the focal side and the healthy side of the patient, and the ratio of FA (rFA) and FA asymmetry (FAasy) will be calculated.

Assessment time points: baseline, and 4 weeks after treatment.

(5) *MBI* will be used to assess patients' ADL. MBI can be used to predict the treatment effect and prognosis of patients. The scale contains 10 assessment tasks, including toileting, bathing, eating, grooming, etc. The total score is 100. Each task is categorized into 5 levels according to the patient's dependence, and each task and level has its corresponding score. The higher the patient's score, the lower the level of dependency, i.e., the greater the ability to live independently (39).

Assessment time points: baseline, and 2 weeks, 4 weeks, 3 months, and 6 months after treatment.

#### 2.6.3. Safety indicators

Incidence of adverse events = (number of patients with adverse events/total number of patients) × 100%.

*Assessment time points:* time of the start of treatment, 2 weeks, 4 weeks, 3 months, and 6 months after treatment.

#### 2.6.4. Adverse events

##### 2.6.4.1. Identification and judgment of adverse events

Adverse events can be any accident, signs, symptoms, diseases, or abnormal test results. These events should be considered adverse events as long as they occur after the intervention, whether or not they are related to the treatment.

*Adverse events of rehabilitation training:* Muscle stretching training may lead to local tissue discomfort, such as pain and swelling, and may even result in fractures in elderly patients with osteoporosis. Postural hypotension or even falls may result when performing postural transfer training. The rehabilitation therapists participating in the study are uniformly trained and skilled and will monitor the patient's blood pressure and heart rate when necessary.

*Adverse events of acupuncture treatment:* Pain, stagnant needles, bent needles, and even infection may occur. The needles should be inserted into the skin quickly to relieve pain. If stagnant needles occur, the needle retention time should be extended appropriately, and the patient should be instructed to relax and massage gently around the needle. If the needle handle is slightly bent, the needle should be slowly lifted out, and if the bending angle is too large, the needle should be lifted out in the direction of the bend. To prevent infection, acupuncture points should be sterilized before acupuncture, and the needle holes should be kept clean after needle removal. The acupuncturists have undergone extensive clinical practice and are able to ensure the safety of acupuncture treatment.

##### 2.6.4.2. Treatment of adverse events

The investigator will determine before each intervention whether the patient is fit to continue treatment and inform the patient of any discomfort during treatment with prompt feedback. Once the patient indicates discomfort, the researcher will immediately stop treatment and assess the patient's signs, symptoms, type, and degree of discomfort, and then decide what to do next.

##### 2.6.4.3. Recording, reporting, and management of adverse events

The researcher will use CRFs to record the adverse events that occurred during the study. If subjects withdraw from the trial due to adverse events, researchers will follow up until the adverse event is resolved. Any adverse events will be reported to the Ethics Committee.

### 2.7. Data collection, management, and monitoring

#### 2.7.1. Data collection

The original data (scale or device assessment results, etc.) of the subjects will be fully collected and recorded in the CRFs in a true, clear, complete and standardized manner. All items in the CRFs will be filled in, and if any content needs to be changed, it should be underlined and the time and reason for the change should be indicated, in addition to a signature next to it.

#### 2.7.2. Data management

All data (documents, evaluation reports, clinical trial results, etc.) will be stored in order in the hospital's archive, where they can be retrieved quickly. These files will be managed by the administrator, anyone can only enter the archives with permission. In addition, paper documents will be scanned and stored encrypted in the computer.

#### 2.7.3. Data monitoring

The inspector will monitor whether the experiments are conducted in accordance with the research protocol and compliance with the relevant regulations, whether there are errors or omissions in the raw data, whether all CRFs are complete and accurate, and whether they deviate from the raw data.

### 2.8. Statistical analysis methods

#### 2.8.1. Data description

The results of the trial will be analyzed according to the intention-to-treat principle. The researchers will collect the follow-up data at each time point, create a database with information and each observed index data of the four groups of cases, and use SPSS26.0 software for statistical analysis. The Shapiro-Wilk method will be used to test the normality of the measurement data, which will be expressed as the mean ± standard deviation (SD) for normal distribution; For non-normally distribution, *M* (*P*_25_*, P*_75_) will be used, and the count data were statistically described using the number of cases and percentages.

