#### 2.2.3. Withdrawal criteria

(1) Patient-initiated withdrawal; (2) Patients who have certain complications or comorbidities during the trial and are not suitable to continue the trial; (3) The patient's condition deteriorates or another stroke occurs and a dangerous event may occur by continuing the trial.

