#### 2.8.2. Analysis methods

The major analysis will be based on the results of the assessment of 4 weeks after treatment. FMA-UE score, SEP-related index, UEFT score, WMFT score, reNSA score, MBI score, and DTI-related data are all measurement data. For within-group comparisons, if the data conformed to normal distribution, paired *t*-test will be used to compare SEP and DTI results, and other data will be performed using repeated measures ANOVA, and least significant different (LSD) methods will be used for pair comparison; for data that do not fit the normal distribution, the Wilcoxon rank-sum test will be used for SEP and DTI results, and the Generalized estimating equation (GEE) approach will be used for all other data. Between-group comparisons will be performed by analysis of variance with a factorial design, and interaction effects and main effects will be analyzed. In addition, Pearson correlation analysis or Spearman's analysis will be used to analyze the correlation among indicators. For the incidence of adverse events among groups, Fisher's exact test will be used. Statistical treatments were all performed using a two-sided test with an inspection level of α = 0.05.

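### Intention-to-treat is stated, but the withdrawal rules take patients out of the trial for outcome-related reasons, so the 4-week comparison may become a selective available-case analysis

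*Protocol article*

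**What the plan says.** Section 2.8.1 sets the principle: "The results of the trial will be analyzed according to the intention-to-treat principle".

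Section 2.2.3 lists three withdrawal criteria. Besides the patient's own decision, they are "Patients who have certain complications or comorbidities during the trial and are not suitable to continue the trial" and "The patient's condition deteriorates or another stroke occurs and a dangerous event may occur by continuing the trial". Both are worded as leaving the trial, not as stopping the intervention.

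Section 2.6.4.3 has the only statement on what happens after withdrawal: "If subjects withdraw from the trial due to adverse events, researchers will follow up until the adverse event is resolved". Neither section says whether the planned outcome visits continue.

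Section 2.8.2 fixes the analysis. The time point is 4 weeks: "The major analysis will be based on the results of the assessment of 4 weeks after treatment". Arms are compared by one method: "Between-group comparisons will be performed by analysis of variance with a factorial design, and interaction effects and main effects will be analyzed". A separate sentence, opening with "For within-group comparisons, if the data conformed to normal distribution", covers change within an arm: SEP and DTI go to a paired test, and "other data will be performed using repeated measures ANOVA, and least significant different (LSD) methods will be used for pair comparison". Non-normal data on those other scales go to GEE.

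**The concern.** Intention-to-treat needs outcomes from everyone randomised, including those who do badly. The withdrawal criteria pick out patients whose neurological or general state has worsened, and such patients will tend to score lower on FMA-UE. If they leave before week 4 and are not assessed, the factorial ANOVA has no value for them and omits them. The remaining arm mean is then too favourable.

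The design is open (section 2.1), and the Discussion accepts that patients, therapists and physicians cannot be blinded. Judgements on who is unsuitable to continue could therefore differ by arm, and unequal loss of this kind biases the comparison.

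This is more than an analysis detail that a later plan can settle. An analysis plan can choose a method for missing values, but it cannot recover an assessment that was never made. Whether withdrawn patients are still seen is a rule of conduct.

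**Working it through.** **1. Who enters which analysis**

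- *4-week factorial ANOVA (between arms):* needs a 4-week value. A patient who misses only week 2, month 3 or month 6 stays in.
- *Repeated measures ANOVA (within an arm; normal data; not SEP or DTI):* as usually run in SPSS, needs all five visits.
- *GEE (within an arm; non-normal data; not SEP or DTI):* does not need all visits.
- *Paired test (SEP, DTI):* needs baseline and week 4, the only two times they are measured.

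To show the difference, assume each of the four post-baseline visits is missed independently with the same probability:

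| Missed per visit (assumed) | In the 4-week ANOVA | Complete for repeated measures ANOVA |
|---|---|---|
| 5% | 0.95 × 136 = 129 | 0.95⁴ = 0.815; × 136 = 111 |
| 10% | 0.90 × 136 = 122 | 0.90⁴ = 0.656; × 136 = 89 |

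The heavier loss in the last column falls on the within-arm results only.

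**2. The plan's own figures (section 2.4)**

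The means are read in the order EG1 41.36, EG2 48.21, EG3 52.87, CG 40.54.

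- Interaction contrast: 52.87 − 41.36 − 48.21 + 40.54 = 3.84, and 3.84 / 4 = 0.96, the stated value.
- Main effect of scalp acupuncture: (48.21 + 52.87 − 41.36 − 40.54) / 2 = 9.59.
- Main effect of intradermal acupuncture: (41.36 + 52.87 − 48.21 − 40.54) / 2 = 2.74.
- Power for the interaction: noncentral F with 1 and N − 4 degrees of freedom and λ = N × (0.96 / 3.38)². This gives 89.95% at 33 per group and 90.8% at 34, so 34 per group reproduces as the number needed with complete data.

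**3. Precision if 4-week values are missing**

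| Lost at week 4 | N left | Interaction power |
|---|---|---|
| 0% | 136 | 90.8% |
| 5% | 129 | 89.3% |
| 10% (the plan's dropout rate) | 122 | 87.6% |
| 20% | 109 | 83.5% |

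**4. Bias if the loss is selective**

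Let *p* be the extra share lost in one arm compared with the other three, and *g* the gap in mean score between those who stay and those who leave. Omitting the leavers raises that arm's mean by *p* × *g*. Each arm enters the interaction contrast with weight ±1 and each main effect with weight ±½. The contrasts therefore move by *p* × *g* and half of that. Equal loss with an equal gap in all arms cancels.

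The documents give neither *p* nor *g*. As assumptions, take *p* = 5% or 10%, and *g* = 1 or 2 planned standard deviations (3.38 or 6.76 points):

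| *p* | *g* | Shift in interaction | Share of 3.84 | Shift in a main effect | Share of 2.74 (intradermal) |
|---|---|---|---|---|---|
| 5% | 3.38 | 0.17 | 4% | 0.08 | 3% |
| 5% | 6.76 | 0.34 | 9% | 0.17 | 6% |
| 10% | 3.38 | 0.34 | 9% | 0.17 | 6% |
| 10% | 6.76 | 0.68 | 18% | 0.34 | 12% |

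Against the scalp main effect of 9.59, the largest of these shifts (0.34) is about 4%.

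**The case against.** The strongest reply is that nothing here says outcome assessment ends at withdrawal. The sentence in section 2.6.4.3 sets a safety duty, and a duty to follow an event to resolution does not forbid later visits. Section 2.8.1, right after the intention-to-treat statement, says follow-up data are gathered at each time point. Deterioration or another stroke is not enough for withdrawal; continuing must also be potentially dangerous. Missing-data handling may stand in an analysis plan that is not shown.

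Most of this stands, and it is why the conclusion is that the comparison *may become* selective, not that it *is*. It does not remove the problem. The criteria are written as leaving the trial, the only stated follow-up after withdrawal ends with the event, and no text ties withdrawn patients back to the planned visits.

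Three stronger readings are tempting and are not supported:

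- *Repeated measures ANOVA decides the trial result and turns it into a completer analysis.* Section 2.8.2 confines it to within-arm comparisons and compares arms by a separate factorial ANOVA. Non-normal data go to GEE.
- *A few dropped patients would outweigh the planned effect.* With an assumed 15-point fall in 2 of 34 patients, one arm's mean moves 2/34 × 15 = 0.88, more than the EG1 minus CG difference of 41.36 − 40.54 = 0.82. That difference is not one of the planned tests, which are the interaction and main effects, and a 15-point fall is about 4.4 planned standard deviations (15 / 3.38).
- *LSD pair comparisons over five visits show bias between arms.* They are made within an arm and say nothing about differences between arms. The protocol also does not say that efficacy will be judged from them.

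**Conclusion.** The point holds in limited form. The intention-to-treat statement and the withdrawal and follow-up rules do not fit together as written. If withdrawn patients are not assessed, the 4-week factorial ANOVA compares available cases, with losses that track the outcome and could differ by arm.

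Under the assumed range, bias in the interaction contrast is 0.17 to 0.68 points, or 4% to 18% of the planned 3.84. It is half as many points in a main effect, and near zero if losses and gaps are alike in all arms. The power cost is small: about 3 percentage points at a 10% loss. These figures rest on the planning means and standard deviation, on the assumed group order, and on assumed extra losses and gaps that the documents do not give. The loss of patients with any missed visit is real but limited to within-arm results for normally distributed outcomes other than SEP and DTI.

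Following the plan as written could give a worse answer than a cheap change would, so it should be changed.

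**What to change.** 1. Reconcile sections 2.2.3, 2.6.4.3 and 2.8.1. State that stopping the intervention does not end outcome assessment: unless the patient withdraws consent, every remaining scheduled assessment is made and used. When treatment is stopped stays as it is. This is the main remedy, and for SEP and DTI, measured only at baseline and 4 weeks, it is the only part that helps.

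2. For the outcomes measured at all visits (FMA-UE, WMFT, UEFT, reNSA, MBI), replace both the separate 4-week factorial ANOVA and the within-arm repeated measures ANOVA with LSD by one linear mixed model. Its terms are scalp × intradermal × visit, with the baseline value as covariate, unstructured covariance, and all observed visits of all randomised patients. Take the 4-week main-effect and interaction contrasts from it.

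The model does not replace step 1. It uses the week-2 value of a patient without a 4-week value, on the assumption that the missing value is predictable from what was observed. A new stroke after week 2 would break that assumption, and a patient with no post-baseline visit adds nothing.

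The cost is continued assessment, at visits already scheduled, of patients who stop treatment, and slightly more modelling work. The named software can fit the model (SPSS MIXED).
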